# CICAFAST: comparison of a biological dressing composed of fetal fibroblasts and keratinocytes on a split-thickness skin graft donor site versus a traditional dressing: a randomized controlled trial

**DOI:** 10.1186/s13063-019-3718-4

**Published:** 2019-10-28

**Keywords:** Wound healing, Split-thickness skin graft, Biological dressing, Fetal cells, Randomized clinical trial

## Abstract

**Background:**

Wound repair is one of the most complex biological processes of human life. Allogeneic cell-based engineered skin substitutes provide off-the-shelf temporary wound coverage and act as biologically active dressings, releasing growth factors, cytokines and extracellular matrix components essential for proper wound healing. However, they are susceptible to immune rejection and this is their major weakness.

Thanks to their low immunogenicity and high effectiveness in regeneration, fetal skin cells represent an attractive alternative to the commonly used autologous and allogeneic skin grafts.

**Methods/design:**

We developed a new dressing comprising a collagen matrix seeded with a specific ratio of active fetal fibroblasts and keratinocytes. These produce a variety of healing growth factors and cytokines which will increase the speed of wound healing and induce an immunotolerant state, with a slight inflammatory reaction and a reduction in pain.

The objective of this study is to demonstrate that the use of this biological dressing for wound healing at the split-thickness skin graft (STSG) donor site, reduces the time to healing, decreases other co-morbidities, such as pain, and improves the appearance of the scar.

This investigation will be conducted as part of a randomized study comparing our new biological dressing with a conventional treatment in a single patient, thus avoiding the factors that may influence the healing of a graft donor site.

**Discussion:**

This clinical trial should enable the development of a new strategy for STSG donor-wound healing based on a regenerative dressing. The pain experienced in the first few days of STSG healing is well known due to the exposure of sensory nerve endings. Reducing this pain will also reduce analgesic drug intake and the duration of sick leave.

Our biological dressing will meet the essential need of surgeons to “re-crop” from existing donor sites, e.g., for thermal-burn patients. By accelerating healing, improving the appearance of the scar and reducing pain, we hope to improve the conditions of treatment for skin grafts.

**Trial registration:**

ClinicalTrials.gov, ID: NCT03334656. Registered on 7 November 2017.

## Background

The skin is the largest organ of the human body with numerous complex functions essential for our survival. Its primary function is to act as a protective barrier against the external environment. It can protect against harmful chemicals, ultraviolet radiation and pathogenic organisms, while at the same time producing vitamin D and regulating body temperature and moisture loss. Loss of the integrity of large portions of the skin as a result of injury, illness or burns can lead to major disability or even death; worldwide, burn injuries affect more than 11 million people annually [1]. Wound repair is one of the most complex biological processes of human life. Skin grafting is one of the therapeutic strategies for covering the wound and limiting morbidity.

Currently, the use of an autologous, split-thickness skin graft (STSG) is commonplace as a reconstructive technique for the permanent closure of excised burns or following the excision of benign or malignant tumors. An STSG involves excision, using a dermatome, of the epidermis and part of the dermis, but leaves behind sufficient reticular dermis in the wound bed to enable the skin to regenerate itself. The greatest disadvantage of this technique is that it creates a donor site that is painful during healing, as well as often unsightly scars. The aim of donor-site management is thus to maintain an environment that promotes optimal healing and prevents morbidity, which can include pain and ultimately delayed healing (for review, see [2]).

Theoretically, an appropriate STSG donor-site dressing should reduce patient discomfort, promote rapid healing, decrease pain, prevent hypertrophic scarring and make it possible to “re-crop” from existing donor sites (which can be a high priority in patients with extensive injuries such as thermal injuries). This is the reason for our interest in this clinical application.

It is both most cost-efficient and in the patient’s best interest for one dressing to be applied and remain in situ until healing is achieved. Unfortunately, if an alginate or hydrofiber dressing is left in situ throughout healing, the dressing is likely to dry out and possibly adhere to the wound bed [3]. Furthermore, two systematic reviews of donor-site dressing found no clear evidence to support the choice of any particular dressing [4, 5] except that they must be moist; occlusive or semi-occlusive dressings both fall into this category.

Currently, cell-based, engineered skin substitutes are showing promise for the treatment of acute and chronic wounds such as deep and partial burns, ulcers resistant to conventional therapies and surgical wounds [6–10]. These various engineered tissue formats include allogeneic fibroblasts and keratinocytes in a bovine collagen matrix (OrCel®, Ortec International, Atlanta, GA, USA) [11] or a bilayered living skin equivalent, Apligraf® (Organogenesis, Inc., Canton, MA, USA). Cultured neonatal fibroblasts derived from the human foreskin are combined with bovine type-I collagen to form a neodermis; this is then seeded with cultured neonatal keratinocytes which proliferate and differentiate [12]. Approved in several countries, Apligraf®, as an allograft, has been used in acute wounds such as surgical excision sites and partial-thickness donor sites [12]. Today, the major disadvantages of this biological dressing are its short shelf-life, its cost, its temporary nature [13] and its susceptibility to immune rejection [14, 15]. Previously, it has not been possible to provide both “seed and soil” in the same therapeutic agent, i.e., a complete epidermal layer has never been obtained (for review, see [16]).

Cutaneous wound healing in the early gestation fetus is remarkably different from healing in adults. The most striking features of the fetal wound response are the speed and the absence of obvious scarring, an observation that was first reported more than 30 years ago [17]. Studies in the marsupial embryo, *Monodelphis domestica,* have shown that this fetal regeneration is not due to the moist, sterile environment of the uterus [18]; rather, the nature of this regeneration mechanism could be the result of the difference between the fetal and adult immune responses [19]. Indeed, in utero, the fetal environment demands that the immune system remains tolerant to maternal alloantigens. After birth, the sudden enormous exposure to environmental antigens, many of them derived from intestinal commensal bacteria, calls for rapid change to adapt distinct immune responses so that they are appropriate for early life. However, a study of adult skin grafted onto a fetus, infused with fetal blood and bathed in amniotic fluid found that the wound healed with scar formation [20]. The conclusion of this study is that scarless healing properties are intrinsic to fetal skin and are not primarily the result of the fetal environment, i.e*.,* immune response and/or sterile fluid. In fact, after 24 weeks of gestation, fetal skin repair is histologically indistinguishable from adult skin. This fetal skin-specific phenotype appears to be dictated by quantitative and qualitative alterations in both the inflammatory and regenerative phases compared to normal adult wound healing, due to molecules secreted by fetal skin cells [21]. Consequently, our hypothesis is that these fetal-skin-cell molecules will have a regenerative effect on adult wound healing.

Fetal wound healing features an absence of acute inflammation in association with a low level of pro-inflammatory chemokines, such as interleukin (IL)-8 [22], and a high level of anti-inflammatory cytokines, such as IL-10. This is the opposite of the situation in adult wound healing [23]. In mice lacking IL-10, fetal wounds display substantial inflammatory cell infiltrates and develop scars.

Furthermore, the fetal fibroblasts proliferate at a faster rate [24], with growth and migration rates decreasing with age [25].

In addition, fetal fibroblasts differ from adult in collagen synthesis, with a huge ratio of collagen type III to collagen type I: 3:1, in contrast to 1:3 in adults [26].

In this regard, a novel acellular collagen matrix derived from fetal bovine dermis has recently been designed for dressing partial- and full-thickness wounds (PriMatrix®, from TEI Biosciences Inc., Boston, MA, USA). However, although this scaffold is particularly rich in type-III collagen [27], it contains no cytokines or growth factor crucial for wound healing.

*The novel nature of our regenerative dressing project* is based on four properties of fetal skin cells, which provide an attractive alternative to the keratinocytes and fibroblasts from neonatal foreskin commonly used as skin substitutes:
Thanks to their low immunogenicity and their immunosuppressive properties they can be used in an allogeneic context without risk of immune rejectionAs a result of the factors they secrete, fetal cells could improve the quality and speed of healing, something which is a constant problem for surgeons. Interestingly, scarless fetal skin healing appears to be largely dependent on the fetal tissue itself and is not reliant on the specific in utero environment [20, 28], giving fetal skin cells great intrinsic potential for wound-healing managementPain is decreased by the anti-inflammatory properties of the secreted factorsFinally, their high proliferation capacity means that from a single skin sample, we can amplify and bank clinical-grade keratinocytes and fibroblasts that can be available to surgeons in 4 days

Furthermore, working on these fetal cells brought us to the conclusion [29] that:
Keratinocytes and fibroblasts can dramatically inhibit allogeneic peripheral blood mononuclear cell (PBMC) proliferation in a dose-dependent manner, confirming that they induce an immunotolerant stateThis immunosuppressive activity of fetal keratinocytes and fibroblasts mainly relies on IDO (indoleamine 2,3-dioxygenase) activity. Through its ability to locally decrease tryptophan availability, IDO is recognized to exert an immunosuppressive effect on T cells requiring tryptophan to proliferateCombining fibroblasts and keratinocytes in co-culture experiments strongly enhances the production of wound-healing growth factors and cytokines (GM-CSF, IL-8, IL-1α, VEGF-A)

These interesting conclusions have led us to build a fetal bioconstruct (biological dressing) that mixes fetal fibroblasts and keratinocytes at a ratio of 1:1 on a type-I collagen matrix (European patent WO 2014 090961A1). This is referred to as CICAFAST, like the trial.

In this trial, the aim of the first application in humans is to test the efficacy of the biological dressing versus a conventional treatment by means of a randomized study. The patient will be their own control, thus avoiding the factors that can influence the healing of a graft donor site. The STSG will be made on the inner part of the thigh at two different sites on the same thigh (upper and lower). The treatment for each site will be chosen by randomization to avoid place bias.

We chose Jelonet® as the conventional dressing since both the Ear, Nose and Throat (ENT) Department and the Burns Center, which are the two investigation centers, use it daily in their practice. Jelonet® (a paraffin-gauze dressing) is the reference treatment for management of the graft donor site. It is essential to differentiate between the graft donor site where a Jelonet® dressing is left in place throughout the duration of healing and the recipient site of the graft or of the wound where the ADAPTIC® (primary dressing made of knitted cellulose acetate fabric and impregnated with a petrolatum emulsion) and UrgoTul® (lipidocolloid dressing) dressings are changed every 24 to 48 h.

This clinical trial should enable the development of a new strategy for STSG donor-site wound healing. The pain of STSG healing during the first days is well known and results from the exposure of sensory nerve endings [30]. Reducing this pain will also reduce the use of analgesic drugs, and sick leave.

Our biological dressing address the essential need for surgeons to “re-crop” from existing donor sites, e.g., for thermal-burn patients. By accelerating healing, improving the appearance of the scar and decreasing pain, we will improve the treatment conditions for skin grafts.

## Methods/design

### Objectives and statistics

#### Objectives

The aim of this trial is to compare wound healing with CICAFAST versus conventional treatment (Jelonet®) in the treatment of STSG donor sites at Day 8 (D8). Success is defined as a mean healing area of 80% or more at D8, as appraised by a physician observer

The secondary objectives are to:
Evaluate the concordance between healing at D8 (or D11 and D15) appraised by the investigator observer and the evaluation of healing by another expert physician using photographs

We would have liked to supplement the photos with the addition of histological and immunohistochemical evidence by performing a biopsy on the patient’s scar, but ethically this was not justifiable. To compensate, we therefore use confocal microscopes to examine the quality of the scar.
Compare the quality of wound healing with CICAFAST versus conventional treatment (Jelonet®) for patients who will be examined using confocal microscopyCompare the speed of wound healing with CICAFAST versus conventional treatment (Jelonet®) in the treatment of STSG donor sitesEvaluate the tolerance of CICAFAST versus conventional treatment (Jelonet®*)* via adverse event (AE) notificationCompare the pain of wound healing with CICAFAST versus conventional treatment (Jelonet®). The patient will note the number of painful days/surgical wound until complete healing in their patient diaryCompare the quality of wound healing with CICAFAST versus conventional treatment (Jelonet®). This will be evaluated using two scales: the Observer Scar Assessment Scale (OSAS) and the Patient Scar Assessment Scale (PSAS) [31]

#### Primary objective and sample size

The primary criterion is success as defined by healing at D8 of more than 80% of the surface area treated. The objective is to demonstrate that the CICAFAST dressing is more effective than the control dressing.

Randomization will be applied for all patients who sign the informed consent form and will be performed on the day of surgical intervention. The randomization pertains to the dressing site position for the patient, where H = High (Top); L = Low. Each patient is their own control.

This balanced block randomization is computer-generated. Subjects are randomized into blocks as the allocation progresses, a block being a subgroup of predetermined size within which there is a random allocation of patients. The software used for the randomization is SAS version 9.4. The randomization key is known to the biostatistician and data managers, to make it impossible for the investigator to assign a particular position for the dressings.

The statistical comparison test used for the primary objective is the McNemar test. We tested the hypothesis that the paired difference score is at least 25% in favor of the CICAFAST compared to the control dressing, and the control dressing is never preferred to the CICAFAST dressing. Using McNemar’s *Z* test, two-sided equality, 38 patients will be required for alpha = 5% and beta = 10% (http://powerandsamplesize.com).

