#### Secondary objectives

Non-parametric paired tests will be used to compare CICAFAST and the control sites.

The statistical analyses will be performed by [name] of Nantes University Hospital. Analyses will be performed using the R statistical software, version 3.5. The alpha risk is set at 5% in a bilateral situation.

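### The primary McNemar test does not use dressing position, the factor that is randomised; a position-adjusted paired comparison would be a small, nearly free gain in efficiency

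*Protocol article*

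**What the plan says.** Each patient has two donor sites on the same thigh, one upper and one lower, and receives one dressing on each. The section Primary objective and sample size states: "The randomization pertains to the dressing site position for the patient, where H = High (Top); L = Low". It adds: "This balanced block randomization is computer-generated". The Background gives the reason: "The treatment for each site will be chosen by randomization to avoid place bias".

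For the binary Day 8 success criterion the article then says: "The statistical comparison test used for the primary objective is the McNemar test". No position term or stratification is attached to it. The sample size rests on two inputs. One is the size of the effect: "We tested the hypothesis that the paired difference score is at least 25% in favor of the CICAFAST compared to the control dressing". The other rules out discordant pairs in the opposite direction, by assuming that "the control dressing is never preferred to the CICAFAST dressing". The resulting number is given as "two-sided equality, 38 patients will be required for alpha = 5% and beta = 10" per cent.

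**The concern.** Position is fixed by design and balanced across patients, but the named test ignores it. Suppose one site heals better than the other. Some pairs are then discordant because of place and not because of the dressing. With balanced allocation these pairs largely cancel in the difference between the two discordant counts, but McNemar still counts every one of them in its variance. The standard error is then too large for the design that was run. The false-positive rate falls below 5%, and power can be lost in the very situation that randomising position was meant to handle. With 38 patients and one binary endpoint, even a few points of power are worth keeping if they cost nothing.

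**Working it through.** **1. The plan's own figure.** Let p10 be the probability that only the CICAFAST site succeeds and p01 that only the control site does. From the article: p10 − p01 = 0.25, p01 = 0, two-sided alpha 0.05, power 0.90.

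n = [(1.960 × √(p10 + p01) + 1.282 × √(p10 + p01 − (p10 − p01)²)) / (p10 − p01)]²
= [(1.960 × 0.500 + 1.282 × 0.433) / 0.25]² = 37.70, rounded up to 38.

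The stated 38 is reproduced.

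**2. Why McNemar is conservative.** Assume no dressing effect. Let u and l be the probabilities that only the upper, or only the lower, site heals; d = u − l and psi = u + l. With exact balance (19 and 19, an assumption), the variance of the discordant difference is 38 × (psi − d²), while McNemar uses 38 × psi. The ratio is 1 − d²/psi. Enumerating all outcomes with psi = 0.25 gives:

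| u / l | 1 − d²/psi | Size, asymptotic McNemar | Size, linear test with position |
|---|---|---|---|
| 0.125 / 0.125 | 1.00 | 0.043 | 0.046 |
| 0.15 / 0.10 | 0.99 | 0.042 | 0.047 |
| 0.175 / 0.075 | 0.96 | 0.039 | 0.049 |
| 0.20 / 0.05 | 0.91 | 0.034 | 0.051 |
| 0.25 / 0 | 0.75 | 0.021 | 0.049 |

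The direction is as feared. The amount is slight unless the position effect is large.

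**3. Power under the planning inputs.** With p01 = 0 and p10 = 0.25 at both positions, exact enumeration gives 0.993 for asymptotic McNemar and 0.993 for the linear test. (The sample-size formula gives 0.90 because it is an approximation; with p01 = 0, four discordant pairs already reject, since √4 = 2 > 1.96.) If p10 is 0.35 with CICAFAST on the upper site and 0.15 on the lower, both tests have 0.994. Even at 0.50 and 0, McNemar has 0.998. Nothing is lost while p01 = 0.

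**4. Power when position creates control-preferred pairs.** Assume (p10, p01) is (0.25 + s, 0) with CICAFAST on the upper site and (0.25, s) on the lower. The mean difference stays at 0.25 and p01 averages s/2.

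| s | McNemar | Linear with position | Gain (points) |
|---|---|---|---|
| 0.05 | 0.882 | 0.893 | 1.1 |
| 0.10 | 0.793 | 0.820 | 2.7 |
| 0.20 | 0.672 | 0.720 | 4.8 |

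Most of the fall down the McNemar column comes from the extra discordance, not from the missing position term. At s = 0.10, McNemar has 0.793; with the same average p01 of 0.05 and no position effect it has 0.789.

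**5. Simulation with an explicit position effect.** Assumed: 38 patients, blocks of 4, logistic model with patient SD 1.5, base logit −0.5, dressing log-odds 0 or 1.5, position log-odds 0, 0.75, 1.5 or 2.25; 20,000 trials per setting. The adjusted test is the two-group comparison of upper-minus-lower differences.

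| Upper-lower difference | Size: McNemar / adjusted | Power: McNemar / adjusted | Gain (points) |
|---|---|---|---|
| 0 | 0.046 / 0.048 | 0.744 / 0.747 | 0.3 |
| about 12 points | 0.043 / 0.051 | 0.721 / 0.737 | 1.6 |
| about 25 points | 0.032 / 0.048 | 0.657 / 0.715 | 5.8 |
| about 36 points | 0.022 / 0.050 | 0.545 / 0.672 | 12.7 |

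Only the gap within a row is due to adjustment. Down the rows the true dressing difference also shrinks, from 0.258 to 0.227. The starting power of 0.744 lies below the planned 90% because this model has about 7% control-preferred pairs before any position effect.

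**6. Which adjusted test.** A re-randomisation test on the same mean difference is not free, because it is discrete. Its power is 0.69 against 0.745 for asymptotic McNemar with no position effect in the step 5 model (5.5 points), and 0.957 against 0.992 under the planning inputs (3.5 points).

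**The case against.** The strongest reply is that nothing is wrong. McNemar never exceeds its nominal level here, and randomising position removes place bias, which is the only purpose the article states. Leaving a balanced nuisance factor out of the test is an efficiency choice. That stands.

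A reader might infer that any upper-lower difference costs power. The documents do not support this: under their own assumption that control is never preferred, step 3 shows no loss at any position effect. The reply has a limit, though. If one site heals better, some patients with the control dressing on that site may heal there and not under CICAFAST, so p01 = 0 is hard to keep alongside a real position effect.

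A reader might also infer that the protocol expects the sites to differ. It says only that position is guarded against. Both sites are on the same inner thigh, and the Discussion describes donor-site depth as constant. The 25- and 36-point differences are therefore assumptions with no support in the text.

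The conservatism also depends on how tightly the blocks balance position. The article gives no block size, and with unrestricted draws McNemar's size stayed at 4.2–5.0% in the same kind of model.

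Finally, position-adjusted sensitivity analyses, and the detail behind "Non-parametric paired tests will be used to compare CICAFAST and the control sites", may sit in an analysis plan that is not shown; their absence is not held against the protocol. The primary test, by contrast, is named outright, so commenting on that choice is fair.

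**Conclusion.** The point holds as a minor efficiency remark. The randomised factor is not used in the primary test. If the sites differ enough to produce control-preferred pairs, McNemar becomes conservative and gives up about 2, 6 or 13 points of power at assumed upper-lower differences of 12, 25 or 36 points. Those sizes rest on the assumed model and on blocks of 4. With no position effect, or with control never preferred, the loss is nil. The two-group adjusted test kept its size at about 5% and was never less powerful than McNemar in the settings examined.

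It would be going too far to conclude that the test is invalid, that the estimate is biased or that 38 is miscalculated. The 38 follows exactly from the stated inputs. Its sensitivity to p01 = 0 (55 patients by the same formula at p01 = 0.05 with the 0.25 difference kept) is a separate matter, and adjusting for position would recover only a small part of it.

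**What to change.** Before the data are analysed, name a position-adjusted primary comparison. For each patient take Day 8 success on the upper site minus success on the lower site (−1, 0 or 1). Compare the mean of this difference between patients with CICAFAST on the upper site and those with it on the lower site, by a two-sample t test or the equivalent linear model with a position term. Report half the difference between the two means as the position-adjusted paired risk difference, with its 95% confidence interval. When the two groups are equal in size this is the same point estimate as the raw paired difference; only the standard error changes. Keep McNemar as a supportive analysis. Do not make a re-randomisation test primary, because its discreteness costs about 4 to 6 points of power against asymptotic McNemar when the position effect is absent or modest.

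The cost is a sentence in the protocol and a few lines of R. Position is assigned through the eCRF, so no new data are needed, and the sample size does not change. The choice must be made in advance, since switching tests after seeing the results would be data-driven.
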